#### Blood tests

The usual blood tests made during acute HF hospitalisation will be performed by the hospital biochemistry laboratory: haemoglobin, K, Na, liver assessment, bilirubin, MDRD [23], NT-pro-BNP, natriuresis, and nutritional tests (C-reactive protein, albumin, prealbumin and orosomucoid), using the AutomateVista 1500 (Siemens HealthCare Diagnostics)]. Renin (Liaison Direct Renin kit, Diasorin), aldosterone (ELISA Kit (E90911Hu), USC N Life Science Inc.), PIIINP (ELISA Kit (E90573Hu), USC N Life Science Inc.), PINP (ELISA Kit (E90957Hu), USC N Life Science Inc.), ICTP (ELISA Kit (E90665Hu), USC N Life Science Inc.) and galectin 3 (ELISA kit (DGAL30), R and D systems) will be analysed at end of trial, after storage at -80°C.

#### QOL scales

It was decided to implement two QOL questionnaires (LHFQ [20] and SF 12[21]) to assess which is more adapted to over-80 year-old HF patients. Both are well-validated and widely used. The SF12 is used on a daily basis in the geriatric department of our hospital and maybe more adapted to the elderly. A second endpoint is to assess the efficiency of this shorter QOL questionnaire, SF12, as compared to the LHFQ, in a very elderly population. They will be completed at inclusion and at 12 month for each subject. QOL scales will be sent to all participants (group A and B) at 6 months (before the 6 month visit for group B) and will be filled in by the patients without any help from medics or paramedics (to avoid bias).

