### The HF-80 Study

#### Objectives and endpoints

The primary objective of this pilot study is to assess optimised HF management, according to the guidelines of the European Society of Cardiology (ESC) [11,12], in terms of impact on QOL in over-80 year-old patients at 6 months.

The secondary objectives are to evaluate the effect of optimised management on:

• Quality of life at 12 months

• Mortality at 12 months

• Readmission for acute HF at 12 months

• Cardiovascular events at 12 months

• Cardiac fibrosis, evaluated by collagen peptides.

The primary assessment criterion is QOL at 6 months, assessed on the Minnesota Living with Heart Failure Questionnaire (LHFQ) [20].

The secondary assessment criteria are QOL at 12 months, measured by both the SF 12 [21] and LHFQ [20] (to check which scale is most suited to this population), mortality at 12 months, number of readmissions for acute HF, cardiovascular events at 12 months, evolution in New York Hospital Association (NYHA) class (at baseline, 6 months and 12 months), and evolution in 6-minutes walking test (6MWT) (at baseline, 6 months and 12 months). Finally, an analysis of the medical and economic interest of this support will be conducted.

This pilot study will also help lay the groundwork for a French national multicentre study of the management of octogenarian HF patients to find what support is most appropriate.

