**Figure 2 F2:**
[figure not shown]
**Flow chart describing HF 80 study investigational procedure**. CE: clinical examination; EKG: electrocardiogram; MMSE: mini mental state examination; QOL: quality of life scale; 6MWT: 6 minutes walking test; Seattle HF: Seattle heart failure score; TTE: transthoracic echocardiography.

• Clinical examination: NYHA class; weight; height; heart rate; blood pressure; right, left or both HF symptoms; triggering factor; cardiovascular risk factors; thyroid pathologies; personal cardiovascular history;

• Quality of life questionnaires (LHFQ [20], SF 12 [21]);

• Six-minutes walking test (6MWT);

• Electrocardiogram (EKG);

• Transthoracic echocardiography (TTE);

• Blood test (haemoglobin, kaliaemia, natraemia, liver assessment, bilirubin, Modification in Diet Renal Disease (MDRD) [23], N-Terminal of pro-Brain Natriuretic Peptide (NT-pro-BNP), and nutritional tests (C-reactive protein, albumin, prealbumin and orosomucoid);

• Renin, aldosterone and collagen peptides [type 1 collagen telopeptide (ICTP), aminoterminal propeptide of type I procollagen (PINP), aminoterminal propeptide of type III procollagen (PIIINP)], and galectin 3;

• Mini mental state examination (MMSE) [24].

During primary hospital care for acute HF and at discharge, both groups will have the same management with initiation of the same treatments, following guidelines [11,12].

Group A subjects will be followed up by their usual GP and cardiologist without any day-hospital care ("usual care" management). The GP and cardiologist will manage treatment optimisation as they are used to doing.

Group B subjects will have the same management as group A but will also receive day-hospital care. The first 3 visits will be at 3 weekly intervals, except in case of unstable HF, and then every 6 weeks for 12 months, to optimise treatment.

During each day-hospital visit in group B, certain data will be recorded to optimise HF management:

• Clinical examination (NYHA class, HF symptoms, blood pressure, heart rate);

• Blood sample (kaliaemia, MDRD [23], NT-pro-BNP);

• Electrocardiogram;

• Optimised treatment doses, if possible, for ACEi, beta-blockers, angiotensin receptor blocker and mineralocorticoid receptor antagonist.

All the visits and contents are described in Table 3.

**Table 3 T3:** Schedule of visits and contents

	Group A		Group B					

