	***Enrollement hospitalization***	***Month 12 visit***	***Enrollement hospitalization***	***Day hospital visits***	***Month 3 visit***	***Month 6 visit***	***Month 9 visit***	***Month 12 visit***

QOL questionnaires (LVHQ, SF12)	X	X	X			X		X

Clinical examination (BP, HR, weight, NYHA)	X	X	X	X	X		X	X

EKG	X	X	X	X	X	X	X	X

6MWT	X	X	X					X

Na, Hb, SGOT, SGPT, Bili	X	X	X					X
K, MDRD, NT-pro-BNP	X	X	X	X	X	X	X	X
PCR, oroso, alb, prealb	X	X	X					X

TTE	X	X	X		X	X	X	X

Blood laboratory	X	X	X		X	X	X	X

Treatments	X	X	X	X	X	X	X	X

BP: blood pressure; HR: heart rate; EKG: electrocardiogram; MMSE: mini mental state examination; QOL: quality of life; 6MWT: 6 minutes walking test; Seattle HF: Seattle heart failure score; TTE: transthoracic echocardiography; CRP: C reactive protein; oroso: orosomucoid; alb: albumin; prealb: prealbumin; MDRD: Modification in Diet Renal Disease; NT-ProBNP: N terminal pro brain natriuretic peptid; K: kaliemia; Na: sodium blood concentration; Hb: hemoglobin; bili: biliubin; SGPT: Serum Glutamopyruvate Transferase, SGOT: Serum Glutamooxaloacetate Transferase.

Patients in both groups will have a notebook, for 12 months. GPs and cardiologists will note all changes in treatment and management.

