### Statistical Considerations

Due to lack of information in the literature concerning the management of over-80 year-old HF patients, it is difficult to estimate correct sample size. The number of subjects to be included is extrapolated from data obtained on younger patients, according to which 40 subjects per group will be included.

With a 2-tailed significance threshold of 0.05, statistical power of 90% and allowing for 15% loss to follow-up, 80 patients will be needed to show a difference of 20 points (σ = 25) in quality of life (LHFQ) at 6 months between the 2 randomisation arms [29]. Morcillo et al. demonstrated that a 20-point difference in LFHQ is significant and feasible in such a population at 6 months' follow-up. An interim analysis is planned. For 34 evaluable patients (17 per group), a difference in QOL score between the 2 arms will be considered significant for an adjusted α equal to 0.003 (Lan and DeMets, EaSt^© ^software). Termination for futility can thus be considered.

The number of patients included and the curve of the inclusions, the theoretical number of visits for the number of patients included, the number of visits actually made and the ratio will be presented for the 2 groups. The cumulative duration of follow-up and the "total follow-up/expected cumulative follow-up" ratio will be calculated.

All analyses will be performed on an intention-to-treat basis. Clinically relevant baseline variables and primary and secondary endpoints will be compared between groups by Chi^2 ^or Fisher-exact tests (categorical variables) and by Student's t tests or Mann-Whitney tests as appropriate (continuous variables). Multivariate analyses to control for confounding effects of variables will be performed.

The survival analysis will be conducted in univariate analysis by log-rank test to compare survival curves following Kaplan-Meier, and in multivariate analysis by the Cox proportional regression model.

To measure the evolution of parameters over time points (visits), longitudinal data analysis will be conducted by ANOVA for repeated measures followed by Tukey-Kramer post-hoc test and by random effects models to measure within-subject correlation taking account of effects over time (random intercept and slope). The impact of covariates, such as randomisation group, will be explored to assess the impact of strategies on QOL score.

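### Non-return of the primary 6-month LHFQ may differ by arm, because only group B has a study visit after the mailing and no common return procedure is stated

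*Protocol article*

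**What the plan says.** All references are to the protocol article.

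- **Endpoint (Objectives and endpoints):** "The primary assessment criterion is QOL at 6 months, assessed on the Minnesota Living with Heart Failure Questionnaire (LHFQ").
- **Collection at 6 months (QOL scales):** "QOL scales will be sent to all participants (group A and B) at 6 months (before the 6 month visit for group B"). The scales "will be filled in by the patients without any help from medics or paramedics (to avoid bias").
- **Group A contact (Investigation Procedure):** "Group A subjects will be followed up by their usual GP and cardiologist without any day-hospital care".
- **Group B contact (same section):** "The first 3 visits will be at 3 weekly intervals, except in case of unstable HF, and then every 6 weeks for 12 months".
- **Schedule (Table 3):** the row "QOL questionnaires (LVHQ, SF12") is ticked for group A at enrolment and month 12. For group B it is ticked at enrolment, at the month 6 visit and at month 12. Group A has no month 6 column.
- **Sample size (Statistical Considerations):** "With a 2-tailed significance threshold of 0.05, statistical power of 90% and allowing for 15% loss to follow-up, 80 patients will be needed". This is a single loss rate, not split by arm.

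**The concern.** The mailing is meant to put both arms on the same footing, and unaided completion is specified as a guard against bias. That guard covers who helps with the form. It does not cover whether the form comes back.

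On return, the arms are placed differently. A group B patient who has not sent the form back has a scheduled hospital visit ahead, and Table 3 attaches the questionnaires to it. A group A patient in the same position has no scheduled study contact until month 12, when a completed form measures the secondary endpoint instead of the primary one. Group B's regular visits may also keep its patients more engaged with the study.

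These patients are over 80, have just been in hospital for acute heart failure, and have an ejection fraction of 35% or less. Failure to return a form could plausibly be related to how ill they are. If such patients are missing more often in one arm, the comparison of returned forms is biased. Inflating the sample for 15% loss restores numbers but does not correct bias. Analysis by intention to treat does not supply values that are missing unequally.

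**Working it through.** **1. The plan's own figure.** Inputs from Statistical Considerations: difference 20, SD 25, two-sided alpha 0.05, power 90%, loss 15%.

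- Normal approximation: n = 2 × 25² × (1.960 + 1.282)² / 20² = 32.8, so 33 per arm. 33/0.85 = 38.8, so 39 per arm and 78 in total.
- Noncentral t: 34 per arm gives 90.2% power. 34/0.85 = 40 per arm and 80 in total.

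The stated 80 is reproduced. Nothing in this point makes the sample size wrong.

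**2. Bias formula.** In one arm, let p be the proportion not returned, M the mean of returned forms, and D the amount by which non-returners score worse than returners. The mean over all patients is (1 − p) × M + p × (M + D) = M + pD. Returned forms alone therefore make the arm look pD points better than it is. With the same D in both arms, the between-arm difference shifts by (p_A − p_B) × D.

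**3. Values.** The article gives no return rates and no gap, so every rate and gap below is an assumption. The first two splits average the plan's 15%; the third averages 22.5%.

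| Non-return A / B | Gap 5 | Gap 10 | Gap 20 |
|---|---|---|---|
| 20% / 10% | 0.5 | 1 | 2 |
| 25% / 5% | 1 | 2 | 4 |
| 40% / 5% | 1.75 | 3.5 | 7 |

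For example, (0.20 − 0.10) × 10 = 1 point, which is 5% of the 20-point target. Likewise (0.25 − 0.05) × 20 = 4 points, which is 20% of it. A 20-point gap is large: it equals the whole design difference, or 20/25 = 0.8 SD.

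**4. Direction.** If non-returners are sicker and more of them are in group A, group A looks too good and a benefit in group B is understated. If non-returners score better than returners, the sign reverses.

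**5. Effect on power** (noncentral t, SD 25, true difference 20).

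- Unequal numbers alone: 34 v 34 gives 90.2%, 32 v 36 gives 90.1%, 30 v 38 gives 89.8% and 24 v 38 gives 85.5%. At the splits that average 15%, almost nothing is lost.
- With 30 v 38 and bias against group B of 1, 2 or 4 points, the expected difference falls to 19, 18 or 16 and power to about 87%, 83% or 73%.

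At those splits the harm comes from the bias and not from the imbalance in numbers.

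**The case against.** The strongest reply is that recovery at the visit is nowhere described. The QOL scales section sets one mode for both arms: the form is mailed, it goes out before group B's visit, and it is completed without staff help. Read that way, the timing is itself a measure to keep the arms alike. Reminder letters, calls and return windows are details that an article commonly leaves to the full protocol, so their absence proves nothing. This stands. A reader might infer that group B forms will be collected at the visit, that group A's unreturned values are lost, and so that non-return will differ. The article supports only that it may.

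The Table 3 tick is also weak evidence. The table has no month 6 column for group A, although a form is mailed to that group then. It also omits group B's 6-month walking test, which the section on that test requires. The tick may simply stand for the postal form. This too stands, but it shows that the table needs reconciling with the text; it does not remove the ambiguity.

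It could be said that group A does have a 6-month contact, because Objectives and endpoints lists NYHA class and the walking test at 6 months without limiting them to one arm. The walking-test section, however, restricts the 6-month test to group B, and Table 3 schedules no such visit for group A.

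The planned random effects models can use baseline and 12-month scores from patients without a 6-month form. That helps, but it does not cure loss that depends on the unseen 6-month state.

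Finally, the sizes are all assumed, and with modest values the bias is about 1 point. That is correct, and the range is shown for that reason.

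**Conclusion.** The concern holds as a risk. As written, the plan gives the two arms unequal opportunity to yield the primary value: both are mailed the form, but only group B has a scheduled study visit after the mailing, with the questionnaires ticked at it. The text and Table 3 also leave open whether a form completed at that visit counts. If it does, the setting differs from group A's as well.

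The size cannot be fixed from the article. Over the assumed splits of 20%/10% and 25%/5%, with gaps of 10 to 20 points, the bias runs from 1 to 4 points against a 20-point design difference. That is not enough to create or remove an effect of the planned size, but 4 points would cut power from about 90% to 73%. The calculation assumes the same gap in both arms; the direction depends on who fails to return the form. Two stronger readings are not supported: that non-return will differ, and that the sample size is wrong. If the full protocol already has identical reminders in both arms, only the correction of Table 3, the recording of return route and the reporting by arm remain.

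**What to change.** 1. Reconcile Table 3 with the QOL scales section: show the month 6 QOL questionnaires as the postal form in both groups, including an entry for group A.
2. State one return window and one reminder procedure, identical in both arms and independent of the day-hospital visit. A second mailing and one scripted call by existing staff would do.
3. Record the date and route of return of every 6-month form.
4. Report return rates by arm, and add a sensitivity analysis that excludes forms returned outside the postal procedure.

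The timing of group B's treatment visit should stay as it is; the fix does not need it moved. Nor should visit-returned forms be dropped from the main analysis, since that would discard primary data in a trial of 40 per arm. The sensitivity analysis shows whether they matter.

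The cost is a little postage and staff time. Because this is a pilot for a national multicentre study, return rates by arm will also help in planning that study.

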### Statistical Considerations

Due to lack of information in the literature concerning the management of over-80 year-old HF patients, it is difficult to estimate correct sample size. The number of subjects to be included is extrapolated from data obtained on younger patients, according to which 40 subjects per group will be included.

With a 2-tailed significance threshold of 0.05, statistical power of 90% and allowing for 15% loss to follow-up, 80 patients will be needed to show a difference of 20 points (σ = 25) in quality of life (LHFQ) at 6 months between the 2 randomisation arms [29]. Morcillo et al. demonstrated that a 20-point difference in LFHQ is significant and feasible in such a population at 6 months' follow-up. An interim analysis is planned. For 34 evaluable patients (17 per group), a difference in QOL score between the 2 arms will be considered significant for an adjusted α equal to 0.003 (Lan and DeMets, EaSt^© ^software). Termination for futility can thus be considered.

The number of patients included and the curve of the inclusions, the theoretical number of visits for the number of patients included, the number of visits actually made and the ratio will be presented for the 2 groups. The cumulative duration of follow-up and the "total follow-up/expected cumulative follow-up" ratio will be calculated.

All analyses will be performed on an intention-to-treat basis. Clinically relevant baseline variables and primary and secondary endpoints will be compared between groups by Chi^2 ^or Fisher-exact tests (categorical variables) and by Student's t tests or Mann-Whitney tests as appropriate (continuous variables). Multivariate analyses to control for confounding effects of variables will be performed.

The survival analysis will be conducted in univariate analysis by log-rank test to compare survival curves following Kaplan-Meier, and in multivariate analysis by the Cox proportional regression model.

To measure the evolution of parameters over time points (visits), longitudinal data analysis will be conducted by ANOVA for repeated measures followed by Tukey-Kramer post-hoc test and by random effects models to measure within-subject correlation taking account of effects over time (random intercept and slope). The impact of covariates, such as randomisation group, will be explored to assess the impact of strategies on QOL score.

Treatment compliance will be analysed initially in a descriptive step and, if necessary, included in multivariate analysis.

A 2-tailed p value of 0.05 will be considered statistically significant (except in interim analysis). All analyses will be performed by STATAv11 (StataCorp, College Station, Texas, USA).

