#### Randomisation

Included patients will be randomly allocated to either arm in a 1:1 ratio. The randomisation list is generated by minimisation [22] to maintain better balance than with traditional block randomisation. Stratification will be performed on gender (female/male), readmission (yes/no) and residence (at home/not at home). When a patient is considered eligible and informed consent has been obtained, randomisation will be performed automatically (on software) by an independent statistician.

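### The interim alpha of 0.003 is an efficacy bound and gives no basis for futility, yet the plan derives futility stopping from it

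*Protocol article*

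**What the plan says.** All of this is in the protocol article, under Statistical Considerations.

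- Sample size: "With a 2-tailed significance threshold of 0.05, statistical power of 90% and allowing for 15% loss to follow-up, 80 patients will be needed". The target is a 20-point LHFQ difference between arms at six months, with an SD of 25.
- Interim: a single look, using 0.003 as the adjusted alpha and citing Lan and DeMets and the EaSt software. The rule reads: "For 34 evaluable patients (17 per group), a difference in QOL score between the 2 arms will be considered significant".
- The sentence that comes directly after this rule: "Termination for futility can thus be considered".
- End of the section: a two-sided p value of 0.05 applies to everything except the interim analysis.

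The article gives no conditional-power limit, beta-spending function or other futility criterion, and it does not mention stopping early for efficacy.

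**The concern.** An alpha-spending threshold controls the false-positive rate when data are tested more than once. Reaching it supports declaring a difference early. Not reaching it only means that the evidence is not yet extreme, which is the usual state of a sound trial at half information. The word that joins the two sentences presents the efficacy threshold as the ground for a futility decision, and that inference is wrong.

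If those running the trial took the text at face value, a trial going exactly to plan could be regarded as a candidate for futility. The trial is open-label and single-centre, and the article gives no other criterion to guide a discretionary decision. The results are also meant to prepare a national multicentre study, so a mistaken futility label could carry beyond this trial.

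**Working it through.** **Inputs** (Statistical Considerations, and Randomisation for the 1:1 ratio): difference 20 points, SD 25 (standardised 0.8), two-sided alpha 0.05, power 90%, loss 15%, 40 per group, interim at 17 per group, interim alpha 0.003. The article does not give the sidedness of 0.003; it is taken as two-sided.

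**1. The planned size reproduces.** Normal approximation: n = 2(1.960 + 1.282)² × (25/20)² = 32.8, so 33 per group; 33/0.85 = 38.8, so 39 per group (78 in total). With the noncentral t, 34 per group; 34/0.85 = 40 per group, exactly 80.

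**2. The 0.003 reproduces as an efficacy bound.** The information fraction is 17/34 = 0.5. O'Brien-Fleming-type spending of 0.025 on each side gives 2 × [2 − 2Φ(2.241/√0.5)] = 0.00305. Under the other common convention (0.05 spent by a single function), half information gives 0.0056, which does not match, while a fraction of 17/40 = 0.425 gives 0.0026, which also rounds to 0.003. Whichever the software used, the figure is an alpha-spending bound for declaring a difference.

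**3. What it takes to reach it.** The standard error at 17 per group is 25 × √(2/17) = 8.57 points.
- Normal: 2.968 × 8.57 = 25.4 points.
- t test, 32 df: 27.5 points.

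Both exceed the 20-point design effect.

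**4. Chance of missing it when the design effect is true.** The expected z is 0.8 × √(17/2) = 2.33.
- Normal: P(reach) = 26.3%, P(miss) = 73.7%.
- Noncentral t: P(reach) = 21.4%, P(miss) = 78.6%.

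With the 20-point effect kept and other SDs assumed, the chance of missing is 52-60% at SD 20 and 85-88% at SD 30.

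**5. What those trials would have gone on to show.** With independent increments and an assumed final critical z of 1.97, P(miss at interim and significant at the end) is about 0.646. Then 0.646/0.737 = 0.876, so about 88% of the design-effect trials that miss the bound would be significant at full size. A simulation of 1,000,000 trials gives 87.7%.

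**6. An interim result exactly on target.** An observed 20 points gives z = 20/8.57 = 2.33, p = 0.020 (0.026 by t test), and misses 0.003. With full-size drift 0.8 × √(34/2) = 3.30, conditional power is 1 − Φ[(1.97 − 2.33 × √0.5 − 3.30 × 0.5)/√0.5] = 97%.

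**7. Worst case for power.** If every trial that missed the bound were stopped, power would equal the chance of reaching it: 21.4% (t) to 26.3% (normal), against 90-91% with 34 evaluable per group.

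**8. A separate futility criterion, for comparison.** Conditional power under the design effect falls below 20% when (1.97 − z × √0.5 − 1.65)/√0.5 > 0.842, which is z < −0.39, or group B observed worse by more than 0.39 × 8.57 = 3.3 points. This stops Φ(−0.39 − 2.33) = 0.3% of trials with a true 20-point effect and Φ(−0.39) = 35% of null trials.

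**The case against.** The strongest reply is that the rule costed above is not in the document. The sentence allows futility to be considered; it does not say that missing 0.003 triggers or justifies a stop. Two kinder readings fit. The connective may point back to the interim look as a whole, which makes a futility discussion possible. Or futility may be a slip for stopping early on a significant difference, the only outcome that the preceding sentence defines. A mechanical stop would also leave the planned 80 patients and the final 0.05 test with little purpose. This stands in part: the 74-79% and 21-26% figures hold only under one reading. It does not rescue the sentence, because under either kinder reading the printed link between this threshold and futility is still wrong or unexplained.

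A second reply is that a futility rule may sit in the full protocol or analysis plan, since an article condenses. That is fair, and its absence here is not the point. The point is the inference that is printed.

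A reader might also infer that a futility stop would lose the 12-month mortality, readmission and quality-of-life data. The article does not support this. It never says that termination would end the follow-up of enrolled patients. Under Trial Status, enrolment starts in October 2011 and completion is estimated for December 2012. If completion means last follow-up (an assumption), 12-month visits leave about three months for enrolment, and all patients would be in before the 34th six-month questionnaire came back.

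**Conclusion.** The point holds as an error of inference in the interim rule. The 0.003 is an efficacy bound, by its wording and by reproduction, and it cannot support a futility decision. If missing it were the criterion, 74% (normal) to 79% (t test) of trials with the true design effect would be open to a futility stop, and about 88% of those would have succeeded. This rests on a 20-point effect with SD 25, half information at 17 per group, a two-sided 0.003 and a final critical z near 1.97.

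A reader might conclude that the trial as planned has only 21-26% power. The documents do not support that: the sentence is permissive, so the figure is a worst-case bound. The defect is worth correcting before the interim analysis, but it does not undermine the sample size or the final analysis.

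**What to change.** State that the 0.003 threshold is for early declaration of efficacy only. Then do one of the following:

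- correct the futility sentence, if early stopping on a significant difference was meant;
- delete it, if no futility stop is intended; or
- base futility on a separate, explicitly non-binding criterion, and give its effect on power.

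One example of the last option is to consider stopping only if conditional power under the 20-point design effect is below 20%. At 17 per group this means group B worse by more than about 3 points. It costs at most 0.3 percentage points of power under the design effect and stops about 35% of null trials. The 20% limit is only an illustration, and the sponsor may choose another. If a futility rule already exists in the full protocol or analysis plan, pointing to it is enough.

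The cost is a change of wording. Sample size, visits and the final test are unaffected.

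### The rule for testing secondary endpoints makes no provision for ordered categories, so NYHA class, read literally, goes to tests that ignore its order and the baseline class

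*Protocol article*

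**What the plan says.** All places are in the protocol article.

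- **Objectives and endpoints** lists among the secondary criteria "evolution in New York Hospital Association (NYHA) class (at baseline, 6 months and 12 months").
- **Statistical Considerations** gives one rule for comparing baseline variables and the primary and secondary endpoints between arms. Categorical variables get chi-square or "Fisher-exact tests (categorical variables"), and the rest get "Student's t tests or Mann-Whitney tests as appropriate (continuous variables"). No ordinal or trend test is named, and NYHA class is not mentioned.
- The same section adds a longitudinal analysis: "To measure the evolution of parameters over time points (visits), longitudinal data analysis will be conducted by ANOVA for repeated measures", followed by random-effects models. The between-arm purpose stated there is the effect on the QOL score.
- **Table 3** schedules the clinical examination, the row that includes NYHA class, at enrolment and month 12 in group A. In group B it is also scheduled at the day-hospital visits and at months 3 and 9, but not at month 6.

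**The concern.** NYHA class runs from I to IV and the order carries the information. If optimised care works, the expected pattern is a shift of the whole distribution towards better classes. A chi-square or Fisher test on the table of arm by class gives the same result however the classes are ordered, so it spreads its power over every kind of difference. It also sets aside the baseline class, although the criterion is worded as an evolution and the baseline is collected. The rank test that would use the order is listed only for continuous variables.

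The stake is modest: one secondary outcome of a pilot. But the article says the pilot should prepare a national multicentre study. An odds ratio for a shift in class would help to plan that study, and a chi-square p-value would not.

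**Working it through.** **1. The plan's own figure.** The only sample size stated is for the LHFQ: "80 patients will be needed to show a difference of 20 points (σ = 25) in quality of life (LHFQ) at 6 months". The assumptions given with it are 90% power, a two-sided level of 0.05 and 15% loss.

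- Normal approximation: n per arm = 2(1.960 + 1.282)² × 25²/20² = 2 × 10.507 × 1.5625 = 32.8, so 33. Then 33/0.85 = 38.8, so 39 per arm and 78 in all.
- Exact t-test: 33.8, so 34 per arm. Then 34/0.85 = 40 per arm and 80 in all.

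The stated 80 reproduces. It concerns the LHFQ only; no power is stated for NYHA class.

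**2. Inputs for NYHA class.**

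- From the article: two-sided 0.05; 1:1 allocation; 40 per arm less 15% gives 34 evaluable. The 15% is stated for the LHFQ at 6 months, so its use at month 12 is an assumption.
- Assumed, because the article gives none: the class distribution in group A and the size of the shift.

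**3. Model of the shift.** Each cumulative odds in group A is multiplied by a common odds ratio (OR). Example: 10/40/40/10% has cumulative proportions 0.10, 0.50, 0.90 and odds 0.111, 1, 9. With OR 3 the odds become 0.333, 3, 27 and the proportions 0.25, 0.75, 0.964. Group B is then 25/50/21/4%.

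**4. Simulated power,** 34 per arm, 3,000 replicates per setting, Pearson chi-square against Mann-Whitney (Wilcoxon) with tie correction. The four-class range covers group A distributions of 10/40/40/10, 5/35/50/10 and 25/25/25/25%; the three-class case is 20/50/30%.

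| OR | Four classes: chi-square | Four classes: rank | Three classes: chi-square | Three classes: rank |
|---|---|---|---|---|
| 2 | 18–24% | 31–36% | 24% | 32% |
| 3 | 45–52% | 64–69% | 55% | 66% |
| 4 | 67–73% | 84–87% | 76% | 84% |
| 5 | 82–84% | 93–94% | 88% | 93% |

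Within each distribution the loss is about 12 to 20 points with four classes at OR 2 to 4, and about 10 to 12 at OR 5. With three classes it is about 5 to 11 points. At OR 1 both tests reject in about 4 to 6% of replicates.

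**5. Two cases outside that pattern.**

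- Only two classes occupied (40/60% against 70/30%): 70% for chi-square, 69% for the rank test, so no loss.
- Non-monotone difference (10/40/40/10% against 25/25/25/25%): 58% for chi-square, 6% for the rank test.

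**6. Analytic check.** For 80% power the noncentrality needed is 7.85 with 1 df, 9.63 with 2 df and 10.90 with 3 df. Where an ordered 1-df test has 80% power, chi-square has about 71% (2 df, three classes) or 64% (3 df, four classes). To regain 80% it needs 9.63/7.85 = 1.23 or 10.90/7.85 = 1.39 times the patients.

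These figures isolate the use of order. Neither Fisher's test nor the gain from adjusting for baseline class was simulated.

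**The case against.** **The plan never assigns NYHA class to chi-square.** This stands. A reader might infer from the rule that the authors chose that test for NYHA class, but the sentence is generic. What can be said is that the rule covers all secondary endpoints, has only two branches, and puts the rank test in the continuous branch.

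**The longitudinal paragraph already covers evolution.** This stands in part. It opens with parameters in general, and a repeated-measures model would use both the order and the baseline value. But it does not name NYHA class, and it would take the steps between classes as equal. As Table 3 is scheduled, month 12 is also the only post-baseline point at which both arms have the examination. The planned multivariate analyses do not name baseline class either.

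**This is detail for an analysis plan, and chi-square is valid.** Type I error is indeed about 5%, so the issue is efficiency, not validity. A fuller document might settle it. But the article is not silent: it states a rule for the endpoints, and that rule lacks a branch for ordered categories.

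**Chi-square has an advantage of its own.** This stands. The article expects that benefit may be offset by comorbidity and iatrogenic complications. If some patients improved and others worsened, chi-square could detect it where a rank test would not.

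**Conclusion.** The point holds as a minor gap in the test rule. Read literally, the rule places NYHA class under tests that ignore its order and the baseline class, and the longitudinal paragraph does not clearly say otherwise.

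A reader might infer that a large part of the power is thrown away. The documents do not support that, because they give no NYHA distribution or effect. The loss is about 12 to 20 points with four occupied classes at OR 2 to 4, about 5 to 11 with three, and none with two. It rests on 34 evaluable per arm at month 12 and on a consistent shift.

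Nor does it follow that a real shift would be found with the better test: at OR 2 the rank test has only about 31–36% power with four classes.

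**What to change.** Add one sentence to Statistical Considerations: NYHA class at month 12 will be compared between arms by a proportional-odds model with arm and baseline NYHA class, or more simply by a Wilcoxon rank-sum test. Keep chi-square and Fisher for unordered or binary variables. If the longitudinal paragraph is meant to cover NYHA class, say so and state how the class is scored.

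The cost is one line of wording and no new data, since both classes are already scheduled in both arms. The downside is reliance on a roughly consistent shift. Showing the full table of classes by arm alongside the model would let a mixed pattern be seen.
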